### Adherence

To determine the adherence to the intervention, individuals will be asked to record their daily consumption of supplements or placebos in a checklist given them by the investigators. To increase compliance and avoid forgetting the use of supplements and placebos, participants will receive messages on their cell phones every day from the investigators’ side. In addition, we will examine serum vitamin D levels at study baseline and at the end of the trial as a measure of compliance.

### Intervention safety

To examine the possible toxicity and hypervitaminosis that might arise from taking vitamin D supplements, serum concentrations of calcium at study baseline and end of trial will be quantified [17].

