### Outcomes

The primary outcomes of the present clinical trial would be serum VDRs, laminin, collagen type IV, hyaluronic acid, MiR-122, MiR-21, and MiR-34a. The secondary outcomes would be liver enzymes, total, direct, and indirect bilirubin, lipid profile, and glycemic indices. We will also examine serum vitamin D and calcium concentrations. All these measurements will be assessed at study baseline and at the end of the trial. Vitamin D supplementation will be considered for the placebo group as post-trial care (Fig. 2).

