### Statistical analysis

Statistical analyses of all data will be performed using SPSS software version 21.0 (SPSS Inc., Chicago, IL, USA). The intention-to-treat approach will be used for data analysis. Data will be expressed as mean ± standard deviations (±SD). The one-sample Kolmogorov–Smirnov test will be used for assessing the normality of the distribution of data. In case of non-normal distribution of a variable, we will apply the log transformation. If the variables were non-normally distributed even, after log transformation, we will use non-parametric tests in the analyses. Repeated measure analysis of variance will be used to identify the effect of the intervention of outcome variables. In these analyses, baseline levels of the outcome variables will be considered as covariates. If any outcome variable was non-normally distributed, we will use the Friedman test. *P* < 0.05 will be considered statistically significant. All analyses will be done by a blind researcher before uncoding the study interventions.

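### The safety section looks for hypervitaminosis through serum calcium alone, gives 25(OH)D only a compliance purpose, and states no per-patient safety result

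*Protocol article*

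**What the plan says.** All references are to the protocol article.

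- **Intervention safety.** The section is one sentence. The aim is "To examine the possible toxicity and hypervitaminosis that might arise from taking vitamin D supplements", and the means is that "serum concentrations of calcium at study baseline and end of trial will be quantified".
- **Adherence.** Besides a daily checklist and phone messages, "we will examine serum vitamin D levels at study baseline and at the end of the trial as a measure of compliance". No other purpose is given there.
- **Outcomes.** After the primary and secondary lists, neither of which contains calcium or vitamin D, the article adds "We will also examine serum vitamin D and calcium concentrations". It attaches no purpose to either analyte.
- **Statistical analysis.** "Data will be expressed as mean ± standard deviations". Then: "Repeated measure analysis of variance will be used to identify the effect of the intervention of outcome variables", with baseline as covariate and non-parametric tests as fallback. A P value below 0.05 "will be considered statistically significant". No count or proportion is mentioned.
- **Participants.** The calculation gives 18 per group, raised to 23 for drop-out.

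**The concern.** Hypervitaminosis is, by its name, an excess of the vitamin. The article itself uses serum 25(OH)D to classify vitamin D status at entry (Inclusion criteria), and it measures vitamin D again at the end. Yet the safety section does not call on that value. Read literally, a participant with a very high final 25(OH)D and normal calcium has a stated place as a good complier and none in the safety result.

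Toxicity also occurs in single patients, whereas the only stated summary describes groups. In arms of 18 to 23, a mean is a poor instrument for isolated cases. At stake is what the trial can say about safety: a plan that states only means and group tests invites the conclusion that an unremarkable mean calcium shows the supplement to be free of toxicity.

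**Working it through.** **1. What the plan computes.** It gives no figure for calcium, 25(OH)D or toxicity, so there is no safety figure to reproduce. The inputs taken from it are n = 18 and n = 23 per arm and the 0.05 level, read as two-sided.

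**2. What must be assumed.** Calcium SD 0.3, 0.4 or 0.5 mg/dL; correlation of baseline with final value 0.5; a rise of 1.5, 2 or 3 mg/dL in each affected patient; k affected patients, all in the vitamin D arm.

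**3. Shift in the mean.** This is k × rise / n. With n = 18 and a rise of 2 mg/dL, one case moves the arm mean by 1 × 2/18 = 0.11 mg/dL and two cases by 2 × 2/18 = 0.22 mg/dL.

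**4. Chance that a group test is significant.** Each setting was simulated 10,000 times, with a t test on final values and with a baseline-adjusted analysis of covariance. The ranges cover both tests, both arm sizes and all assumed SDs and rises.

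| Affected patients | Proportion of trials with P < 0.05 |
|---|---|
| 0 | about 5% |
| 1 | 1-5% |
| 2 | 5-9% |
| 3 | 13-21% |
| 5 | 31-91% |

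**5. Why a larger rise does not help.** An outlier raises the pooled SD along with the mean. For the unadjusted t test, let the rise d become large against the SD. The difference in means is kd/n. The pooled variance tends to d²k(n−k)/[2n(n−1)]. The t statistic therefore tends to √[k(n−1)/(n−k)]. With n = 18:

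- k = 1: √(17/17) = 1.00
- k = 2: √(34/16) = 1.46
- k = 3: √(51/15) = 1.84
- k = 5: √(85/13) = 2.56

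The critical value on 34 degrees of freedom is about 2.03. Up to three very extreme cases do not reach it; five do. This part does not depend on the assumed SD.

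**6. What counting would show.** Every affected patient sampled at the end visit is visible in a count. The chance of at least one case in 23 is 1 − (1−p)^23, which is 21%, 37%, 69% and 91% at true rates p of 1%, 2%, 5% and 10%.

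**7. What zero cases would exclude.** The exact two-sided 95% upper limit is 1 − 0.025^(1/n).

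- n = 18: 1 − 0.025^(1/18) = 18.5%
- n = 23: 1 − 0.025^(1/23) = 14.8%

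The one-sided 95% limits, 1 − 0.05^(1/n), are 15.3% and 12.2%.

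**The case against.** A reader might infer that safety will be decided by a P value on mean calcium, so that toxic cases would almost always be reported as no signal. The article does not support this.

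- The safety section says only that calcium will be measured. The analysis of variance is written for outcome variables, and calcium is in neither the primary nor the secondary list. Nothing says that individual values will go unread.
- Almost always would also be too strong: it fits one or two cases, not a cluster of five.
- It would likewise go too far to say that 25(OH)D is used for nothing but compliance. The Outcomes section lists it beside calcium without restricting its use. What can be said is that compliance is the only purpose stated.

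Two further objections stand in part. Laboratory limits and safety listings are commonly left to a full protocol or analysis plan, so their absence from an article is not in itself a fault. And the choice of calcium rests on a cited source that is not at hand; nothing here says that calcium is the wrong marker. The zero-case limits reflect sample size and would be the same under any analysis. They bear on how the conclusion is worded, not on the choice of marker.

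What remains is more than missing detail. The article fixes the aim, the single safety marker, the purpose of the other assay and the only form of summary, and these do not fit together well.

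**Conclusion.** The point holds in a limited form. The stated safety aim is tied to calcium alone, although 25(OH)D is available at both time points, and no stated summary would display individual cases. If calcium were reported only as means with group tests, one or two affected patients would be picked up in about 1-9% of trials, hardly different from the 5% expected by chance. That range depends on the assumed SD, rises and correlation, none of which is in the article. The limiting argument in step 5 shows why the result for isolated cases is not sensitive to them. No primary or secondary outcome is affected. The change is worth making because it puts data already collected to better use.

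**What to change.** 1. **Intervention safety:** state that end-of-trial 25(OH)D is read for safety as well as for compliance.
2. **Statistical analysis:** report by arm the number and percentage of participants above the laboratory's upper limit for calcium and for 25(OH)D, with exact two-sided 95% confidence intervals. Give the number with an end-of-trial sample as denominator. Keep means and SDs as description.
3. **Conclusion:** limit any no-toxicity statement to rates that the interval excludes.

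The laboratory limit serves here for reporting only; no dose, treatment or stopping rule is proposed. The cost is a few sentences and one small table, with no extra sampling. The price is a more modest safety statement: even with no cases at all, a rate of up to 18.5% (18 patients) or 14.8% (23 patients) would remain possible.

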### Inclusion criteria

In this study, we will recruit NAFLD patients with NASH aged 20–60 years, at least six months before enrollment in the study. Diagnosis of fatty liver will be made based on findings from ultrasound reports. Patients will be recruited if they had NAFLD at grade 2 or 3. Having a vitamin D deficiency or insufficiency (serum levels of 25 (OH) vitamin D_3_ < 30 ng/mL) would be another requirement for inclusion in the study [13].

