### Exclusion criteria

Individuals who are smokers, those consuming alcohol, are pregnant or lactating, or decided to get pregnant during the next three months will not be included. We also will not include individuals with some pathologic conditions affecting the liver, including viral hepatitis, any acute or chronic liver failure, liver transplantation, cholestasis, hemochromatosis, Wilson disease, α-1 anti-trypsin deficiency, suffering from diabetes, heart failure, renal failure, kidney stones, any neoplasia, inflammatory disease, usual consumption of corticosteroids, non-steroidal anti-inflammatory drugs (NSAIDs), antibiotics, proton pump inhibitors (PPIs) during the last nine months, hormone replacement therapy (HRT) or those taking high doses of estrogen, vitamin D supplements, and antioxidants during the last three months. If a participant gets pregnant during the study, consumes alcohol and/or tobacco, antioxidants, or has weight loss of > 2 kg, he or she will be excluded.

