### Intervention

All patients, researchers, gastroenterologist, statistical analyst, and laboratory staff will be blind to intervention. According to the protocol of vitamin D deficiency and insufficiency treatment [13], the supplementation procedure for vitamin D will be set at a 4000 IU tablet per day for 12 weeks. The experimental group will receive 4000 IU vitamin D supplements daily with their main meals for 12 weeks. The placebo group will take placebo tablets containing lactose, which are similar to vitamin D tablets in appearance, shape, color, and smell. Participants in the placebo group will also be requested to take the tablet with their main meals for 12 weeks. The vitamin D and placebo tablets will be produced by the PARS MINOO Co., Tehran, Iran. The quality control of vitamin D tablets will be determined by the HPLC method. All patients will be blind for grouping till the end of the trial. A third person that is not involved directly in the study will package the vitamin D and placebo tablets in the bottles. The bottles will be coded as A and B and will remain unknown to researchers until the end of study. Patients will take their bottles in two time periods: at their first visit and in the middle of trial at week 6 in the laboratory of Cellular and Molecular Nutrition.

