### Blood sampling, biochemical, and molecular measurements

In a fasting state, a 10-mL venous blood sample will be taken from each patient between 07:00 and 09:00 hours. The samples will be immediately centrifuged at 20 °C, 3000 rpm for 10 min in aseptic condition. Serum samples will be separated in RNAase free micro-tubes in the clean room, where all equipment will be UV exposed for 20 min. Then the samples will be stored at − 70 °C. Serum lipid profiles (TC, HDL, LDL, TG), liver markers (ALT, AST, total, direct and indirect bilirubin), glucose, and calcium levels will be measured by the enzymatic colorimetric method using commercial kits. Serum insulin, vitamin D, VDR, laminin, collagen type IV, and hyaluronic acid will be measured using an enzyme-linked immunosorbent assay (ELISA) kit. Insulin resistance and insulin sensitivity will be determined using the HOMA-IR and QUICKI equations, respectively [19].

The gene expression of serum MiRs (MiR-122, MiR-21, and MiR-34a) will be determined by real-time polymerase chain reaction (PCR).

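### Baseline serum calcium, the only named toxicity check, is planned but not used by the listed entry criteria, so a patient with raised calcium could start 4000 IU/day

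*Protocol article*

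**What the plan says.** All references are to the protocol article.

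- **Intervention safety** gives toxicity and hypervitaminosis as the risk and assigns one measurement to it: "serum concentrations of calcium at study baseline and end of trial will be quantified". **Outcomes** confirms the timing for all variables, calcium included: "All these measurements will be assessed at study baseline and at the end of the trial".
- **Inclusion criteria** use one serum result. A 25(OH)D below 30 ng/mL "would be another requirement for inclusion in the study".
- **Exclusion criteria** cover diagnosed conditions close to calcium risk ("suffering from diabetes, heart failure, renal failure, kidney stones, any neoplasia, inflammatory disease") and vitamin D supplements in the previous three months. Neither serum calcium nor hypercalcaemia is listed. The on-study exclusion rules (pregnancy, alcohol or tobacco, antioxidants, weight loss above 2 kg) do not mention calcium either.
- **Study design** places the fasting blood draw in the work-up before allocation. **Blood sampling** describes centrifugation and separation, and continues: "Then the samples will be stored at" −70 °C. It does not say when calcium is assayed relative to allocation.
- **Intervention** sets 4000 IU daily for 12 weeks. The only mid-course contact it describes is bottle collection: "Patients will take their bottles in two time periods: at their first visit and in the middle of trial at week 6".

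**The concern.** A baseline value of a safety marker has two uses: it is the reference for the end-of-trial value, and it can keep out a patient for whom the treatment is unsuitable. The text provides for the first use only. The neighbouring exclusions (renal failure, kidney stones, neoplasia) depend on a known diagnosis, so an unrecognised raised calcium would pass them.

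At stake is the safety of an individual patient, not the validity of the comparison. Someone who enters with raised calcium could take vitamin D daily for the whole course, and the next scheduled calcium result would come when no tablets remain. The information needed to avoid this comes from a test the trial has already decided to do, on blood drawn before allocation.

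**Working it through.** The plan states no figure on this point, so there is none to reproduce. The check sets the sections side by side and then sizes the exposure and the cost.

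**1. Does any listed rule use calcium?** Inclusion: no. Exclusion at entry: no. On-study exclusion: no. Calcium appears only as a measurement, at two time points.

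**2. Could the baseline value be available in time?** Yes. The sample is drawn before allocation (Study design), and entry already waits for one serum result, 25(OH)D (Inclusion criteria). What is missing is a rule that calcium be read then. Storage at −70 °C leaves open that it is assayed later, in batches.

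**3. Exposure of a patient admitted with raised calcium and allocated vitamin D.**
- Days: 12 × 7 = 84.
- Dose before the first scheduled post-dose calcium: 84 × 4000 = 336,000 IU.
- With 23 of 46 patients in each group, the chance that such a patient is allocated vitamin D is 23/46 = 50%.

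**4. How many such patients?** The documents give no rate. For a rate r among otherwise eligible patients the expected number is 46 × r, half of them on vitamin D. No value of r can be defended from the text.

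**5. Cost of the entry rule in patients.** Assumption: 1% to 2.5% of unaffected people exceed the laboratory's upper limit at a single reading.
- Chance highs among 46: 46 × 0.01 = 0.46 to 46 × 0.025 = 1.15. This is also the expected number of repeat tests in unaffected patients.
- High on both readings, if independent: 46 × 0.01² = 0.0046 to 46 × 0.025² = 0.029.
- High on both, bivariate normal with correlation 0.5 to 0.7 (assumed): 0.06 to 0.12 at the 1% rate and 0.21 to 0.38 at the 2.5% rate.

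So without a repeat about one patient per 46 is lost at most, and with a repeat fewer than 0.4. The plan screens 300 patients, so a replacement should be available.

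**6. Would a week-6 calcium be as clear a gain?**
- Half the course would remain: 42 × 4000 = 168,000 IU taken, and 42/84 = 50% of tablets still to come.
- Assumption: 0.5% to 5% of the 23 vitamin D patients have truly raised calcium by then. Expected cases: 23 × 0.005 = 0.115 to 23 × 0.05 = 1.15.
- At the low end, chance highs among all 46 outnumber true cases by 0.46/0.115 = 4 to 1.15/0.115 = 10 to one.
- At the 2.5% rate with correlated readings, wrong stops after a repeat (0.21 to 0.38) still exceed 0.115 true cases.

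The balance therefore depends on a rate the documents do not supply.

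**The case against.** The strongest reply is that this reports something absent from a condensed article. Calcium limits, adverse-event handling and stopping rules commonly sit in the full protocol, and the time-point figure is not shown. The population is also already restricted: low 25(OH)D is required, and renal failure, kidney stones, neoplasia, inflammatory disease and recent vitamin D use are excluded. The dose and the calcium check cite sources that are not at hand.

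Much of this stands. It limits the point to the listed criteria and keeps the likely benefit small. It does not remove the point, because the article sets out its entry criteria in detail, including a laboratory threshold, and plans the calcium test without giving its baseline result any role at entry.

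A second objection also stands: excluding on one unconfirmed high value would turn away mostly unaffected people, so a repeat reading is needed.

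A reader might infer more, namely that the two-point schedule is itself unsafe or that a mid-trial calcium is required. The documents do not support that. The schedule is explicit and consistent, symptoms or clinical judgement could still stop the tablets, and no hypercalcaemia rate is given. A week-6 test would also need a new draw and a prompt reading at a visit described only for bottle collection. It carries a blinding risk too: "The bottles will be coded as A and B and will remain unknown to researchers until the end of study", so one confirmed high value linked to a code could suggest the allocation of all 46 patients. An outside reader would reduce that risk, but at the price of keeping a confirmed high calcium from the study's own clinicians.

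**Conclusion.** The point holds in a limited form and is worth considering. The only named toxicity marker is planned at baseline, yet no listed criterion acts on it, so a patient with already raised calcium could be allocated 84 days of 4000 IU (336,000 IU in total). How often this would happen cannot be estimated from the documents, and the existing exclusions make it uncommon rather than impossible. The cost of closing the gap is at most about one replaced patient per 46, on the assumed 1% to 2.5% chance-high rate, and less after a repeat. The text does not support calling the schedule contradictory, or saying that calcium cannot be known before allocation; it simply does not require that it be known. The absence of a post-dose calcium before the end of the course is a fact of the schedule, but a week-6 test remains an option, not a necessary correction.

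**What to change.** Add to the entry criteria: serum calcium is measured before allocation on a fresh portion of the baseline sample, before the remainder is frozen, and is read together with 25(OH)D. A patient above the laboratory's upper limit of normal has a repeat reading, preferably on a new sample, and is not enrolled if it is again high.

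**Cost.** The assay is already planned, but it must be run patient by patient before allocation. About 0.5 to 1.2 repeat tests per 46 are expected in unaffected patients, and at most about one otherwise eligible patient per 46 is replaced. Because the decision precedes allocation, blinding, the intention-to-treat analysis and the sample size are unaffected.

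**Timing.** Recruitment was due to finish on 15 January 2019 and the article appeared on 4 March 2019. On those dates the change can help only if recruitment overran.

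**Optional.** A calcium test at the week-6 bottle visit may be considered, if the sponsor accepts up to 46 extra draws, an outside reader and the blinding risk.

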### Outcomes

The primary outcomes of the present clinical trial would be serum VDRs, laminin, collagen type IV, hyaluronic acid, MiR-122, MiR-21, and MiR-34a. The secondary outcomes would be liver enzymes, total, direct, and indirect bilirubin, lipid profile, and glycemic indices. We will also examine serum vitamin D and calcium concentrations. All these measurements will be assessed at study baseline and at the end of the trial. Vitamin D supplementation will be considered for the placebo group as post-trial care (Fig. 2).

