## Methods/design

### Participants

This parallel randomized double-blind placebo-controlled clinical trial (RCT) will be done on patients with NASH. Patients will be recruited from the Masoud Internal Specialized Clinic and Imam Khomeini Hospital, affiliated with Tehran University of Medical Sciences, Tehran, Iran. We calculated required sample size based on data from a previous study [12] by considering serum laminin as a key dependent variable, type I error of 0.05, and study power of 90%. Considering the mean difference in serum laminin levels of 136.7 ng/mL between the two groups [12], based on the suggested formula for parallel clinical trials, we reached the sample size of 18 patients in each group. Taking into account a possible drop-out rate of 30%, 23 patients will be enrolled in each group. The study is registered in the Iranian Registry of Clinical Trials website (http://www.irct.ir, identifier: IRCT201405251485N13). This study was reported based on recommended check lists for clinical trials (Additional files 1 and 2).

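### Seven unranked primary outcomes share one P < 0.05 criterion while the trial is sized on laminin alone, so the family-wise error over the primary set is not held at 5%

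*Protocol article*

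**What the plan says.** Three statements in the protocol article bear on this point.

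- **Outcomes:** "The primary outcomes of the present clinical trial would be serum VDRs, laminin, collagen type IV, hyaluronic acid, MiR-122, MiR-21, and MiR-34a". This is one list of seven, with no order and no statement of how many must succeed.
- **Statistical analysis:** one model serves all outcomes ("Repeated measure analysis of variance will be used to identify the effect of the intervention of outcome variables"), and one criterion follows: P "< 0.05 will be considered statistically significant". No adjustment or hierarchy accompanies it.
- **Participants:** the trial is sized "by considering serum laminin as a key dependent variable", with a type I error of 0.05 and 90% power. The input is given as "Considering the mean difference in serum laminin levels of 136.7 ng/mL between the two groups", and the result as "we reached the sample size of 18 patients in each group". Enrolment is 23 per group after an allowance for drop-out. No standard deviation and no sidedness are stated.

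**The concern.** The sample-size paragraph treats laminin as the variable that matters, while the outcome list gives it the same standing as six others. The design calculation is for one comparison. The primary analysis consists of seven.

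The Discussion (and the abstract) promises a trial-level conclusion about whether vitamin D controls liver fibrosis. Nothing in the article says which marker, or how many, must reach significance to support it. A single microRNA with P below 0.05, alongside a null laminin result, could therefore be reported as a positive primary finding. The chance that such a finding is false is several times the 5% that a reader would take from the sample-size paragraph. For the six markers other than laminin, the article gives no power at all.

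**Working it through.** **Inputs from the protocol article.** Seven primary outcomes (Outcomes); threshold 0.05 (Statistical analysis); laminin difference 136.7 ng/mL, error 0.05, power 90%, 18 per group, 23 enrolled per group (Participants).

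**Inputs assumed.** Two-sided tests, and the correlations between the seven test statistics. The standardised effect for laminin is back-solved from the stated sample size, because no standard deviation is given.

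**1. The plan's own figure.** The 18 per group cannot be reproduced independently without a standard deviation. Solved backwards with the normal approximation:

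- d = (1.960 + 1.282) × √(2/18) = 1.08
- implied SD = 136.7 / 1.08, about 126.5 ng/mL

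The same step with the t distribution gives d of about 1.11. A one-sided test would imply an SD of about 140 ng/mL. These are consequences of the stated 18, not a check of it.

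**2. Family-wise error if vitamin D affects none of the seven.**

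- Independent tests: 1 − 0.95^7 = 1 − 0.6983 = 0.302
- Upper bound under any dependence: 7 × 0.05 = 0.35
- Equal positive correlation (assumed; simulation of seven two-sided z-tests, 1,000,000 draws):

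| Pairwise correlation | Chance of at least one false positive |
|---|---|
| 0 | 30% |
| 0.3 | 27% |
| 0.5 | 23% |
| 0.7 | 18% |
| 0.9 | 11% |

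**3. If vitamin D truly affects some markers.** Only the unaffected ones can give false positives. Under independence, six unaffected markers give 1 − 0.95^6 = 26.5%, four give 18.5% and three give 14.3%.

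**4. Laminin power if all seven stay primary.** The strictest step of Holm is the Bonferroni level, 0.05/7 = 0.00714, with a two-sided critical value of 2.690.

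- 18 per group, normal approximation: Φ(1.0805 × √(18/2) − 2.690) = Φ(0.551) = 71%. The t-based figure with d = 1.11 is 68%.
- 23 per group, normal approximation: Φ(1.0805 × √(23/2) − 2.690) = Φ(0.974) = 83%. The t-based figure is 82%.
- For 90% power: 2 × (2.690 + 1.282)² / 1.0805² = 27.02, so 28 evaluable per group.

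**5. Laminin as the single primary.** The error stays at 0.05 and the 18 per group is unchanged. If the other six were tested by Holm at 0.05 without first requiring laminin to be significant, there would be two separate 5% families. Error over all seven could then reach 1 − 0.95² = 9.75% if the families are independent. If they are tested only after a significant laminin result, the total is held at 5%.

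**The case against.** The strongest reply is that multiplicity is commonly left to a statistical analysis plan, that none is shown, and that the significance sentence is generic. It does not say that each primary outcome is tested without correction. This has some force: the absence of an adjustment method would not be a finding by itself. But the article does not merely stay silent. It fixes seven equal primary outcomes, one threshold, and a sample size for one of them. A later plan would have to override one of these statements.

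A second reply is that the objective names several markers, which can be read as separate questions, and not every statistician would require family-wise control for those. That is fair, but the article calls all seven primary, never calls itself exploratory, and draws one overall conclusion about fibrosis.

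Three stronger readings are tempting and should be resisted.

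- A reader might infer that the 5% type I error holds for laminin only. It does not follow: each marker's own test has a nominal 5% error. What is lost is control over the set. Only the 90% power is specific to laminin.
- A reader might take 30% as the trial's actual false-positive rate. It is the figure for independent tests with no effect on any marker. Positive correlation lowers it, and 35% is the bound without any assumption on dependence.
- A reader might infer that the protocol declares success on any one marker. It states no success rule. It leaves that reading open.

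Blinded analysis before the codes are broken does not answer the point. It guards against biased choices, not against chance findings across seven tests.

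**Conclusion.** The point holds as a conflict within the article: seven unranked primary outcomes at one 0.05 threshold, against a design built on laminin. The family-wise error over the primary set is not held at 5%. Across assumed correlations from 0 to 0.7 it runs from 30.2% down to about 18%, provided that vitamin D affects none of the markers and any one significant result counts as success. Even at a correlation of 0.9 it is about 11%, more than twice the nominal level. The correlations are assumptions, because the article gives none. The power figures rest on an effect size back-solved from 18 per group at 90% power, two-sided. They describe what a correction would cost laminin, not a harm of the plan as written.

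**What to change.** Before bottles A and B are uncoded, issue a dated amendment, update the registry entry and disclose the change in the report:

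1. Name serum laminin as the single primary outcome, tested at two-sided 0.05.
2. Make VDR, collagen type IV, hyaluronic acid, MiR-122, MiR-21 and MiR-34a key secondary outcomes. Test them by Holm, or in a stated fixed order, only if laminin is significant. Otherwise report them as exploratory.

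The choice of laminin is not driven by data, since the sample-size paragraph already singles it out. No patient, visit or assay changes, and the 18 per group calculation stands. The timing is feasible on the stated schedule: recruitment was due to end on 15 January 2019, so the last 12-week course would end about 9 April 2019, after publication on 4 March 2019.

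The cost is real. Six markers can no longer each support a primary claim, and changing primary outcomes this late has to be openly declared.

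An alternative that demotes nothing is Holm across all seven, with the laminin power restated. At the strictest step that power is about 68–71% with 18 per group and about 83% with 23, on the assumptions given above.
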